## Abstract

**Background:**

Postnatal depression can have a substantial impact on the woman, the child and family as a whole. Thus, there is a need to examine different ways of helping women experiencing postnatal depression; encouraging them to exercise may be one way. A meta analysis found some support for exercise as an adjunctive treatment for postnatal depression but the methodological inadequacy of the few small studies included means that it is uncertain whether exercise reduces symptoms of postnatal depression. We aim to determine whether a pragmatic exercise intervention that involves one-to-one personalised exercise consultations and telephone support plus usual care in women with postnatal depression, is superior to usual care only, in reducing symptoms of postnatal depression.

**Methods:**

We aim to recruit 208 women with postnatal depression in the West Midlands. Recently delivered women who meet the ICD-10 diagnosis for depression will be randomised to usual care plus exercise or usual care only. The exercise intervention will be delivered over 6 months. The primary outcome measure is difference in mean Edinburgh Postnatal Depression Scale score between the groups at six month follow-up. Outcome measures will be assessed at baseline and at six and 12 month post randomisation.

**Discussion:**

Findings from the research will inform future clinical guidance on antenatal and postnatal mental health, as well as inform practitioners working with postnatal depression.

**Trial registration number:**

ISRCTN84245563

## Background

It is estimated that depression will be the second most common cause of disability worldwide by 2020 [1]. Postnatal depression (PND) is a serious problem across cultures and affects about 10-15% of women some time in the year after giving birth [2,3]. Women with postnatal depression can experience disabling symptoms of low mood, irritability, fatigue, insomnia, changes in appetite, anxiety, guilt, inability to cope, feelings of worthlessness and thoughts of suicide. Frequently exacerbating these symptoms are low self-esteem, lack of confidence, and unrealistic expectations of motherhood. Women who have PND are twice as likely to experience subsequent episodes of depression in later life [4]. PND has health consequences not only for the mother but also for the child and family as a whole. Cognitive and emotional development and social behaviour have been shown to be adversely affected in children whose mothers have PND [5]. PND can cause impaired maternal-infant interactions and negative perceptions of infant behaviour [6]. Marital difficulties are not uncommon and the partner may also become depressed [7]. Suicide is a rare but devastating consequence of PND.

After giving birth, many women have excess weight and decreased fitness levels [8,9]. New mothers have reported weight gain to be a significant concern for them [10]. Studies of pregnant and postpartum women have indicated they are at high risk for inactivity and reductions in previously established levels of activity [11]. These health concerns would also apply to women with PND. The new physical activity guidelines “Start Active Stay Active” published by the Chief Medical Officers in the UK [12] state that participation in physical activity can have an important role in promoting mental health and well-being. Meta-analyses and reviews [13-15] have concluded that exercise may be effective in reducing depression in adult populations, although concerns have been raised about the methodological quality of trials to date. On the basis of the available evidence in 2009 [16] the National Institute for Health and Clinical Excellence (NICE) in England recommended that people with persistent sub-threshold depressive symptoms or mild to moderate depression should be advised of the benefits of exercise.

Based on evidence of the positive effects of exercise on depression in general populations it seems plausible that regular exercise may also be an effective intervention for the treatment of PND. However, direct extrapolation from research with general populations to those experiencing PND is not necessarily appropriate because the circumstances of early motherhood are sufficiently different to preclude this. Based on general population evidence and findings from two very small trials (total n = 39) that recruited women with PND, in 2006 NICE [17] recommended in their guidance on the management of antenatal and postnatal mental health, that health professionals should consider exercise as a treatment for PND.

A systematic review and meta-analysis [18] of randomised and quasi randomised controlled trials has examined the effects of exercise on PND. Five trials (six reports) [19-24] were identified (total N: n = 114 intervention; n = 107 comparators). In three trials, participants were receiving antidepressant medication and/or psychological therapies, one trial excluded participants if they were currently using antidepressants or receiving psychotherapy and one did not provide this information. When compared with no-exercise, exercise significantly reduced symptoms of PND (weighted mean difference in Edinburgh Postnatal Depression Scale [25] score was −4.00 points (95% CI: -7.64 to −0.35)) (standardised mean difference: -0.81 (95% CI: -1.53 to −0.10)). Whilst the magnitude of this effect might appear initially encouraging, caution is required when interpreting this finding because significant heterogeneity was found and because the effect size was reduced considerably (and became non-significant) when the trial [20] that included exercise as a co-intervention with social support was excluded (standardised mean difference = −0.42 (CI:-0.90 to 0.05)). Heterogeneity was no longer present either. Therefore it is uncertain whether exercise reduces symptoms of PND and the significant effect size of −0.81 is contingent on the inclusion of one trial where exercise was a co-intervention. We should also remain cognisant that trials were small, confidence intervals were wide, had limited follow-up and included samples of volunteers and not clinically defined cases according to diagnostic criteria. There were no studies on long term effectiveness. Given the paucity of high quality research, it is necessary to evaluate more fully the effectiveness of exercise as a treatment for PND.

In summary, a large trial that compares exercise with standard treatment(s) and which includes longer term follow-up is now essential given the recommendation from NICE [17] that health professionals should consider exercise as treatment for PND. We are aware of no ongoing trials in this field and therefore the proposed research has the potential to make a significant contribution to the literature. No previous research has investigated the views of depressed postnatal women participating in exercise programmes and a qualitative study will be nested within this trial. The qualitative study will aid our understanding why exercise, in addition to usual care, was or was not superior to usual care in reducing symptoms of PND. These insights could subsequently inform clinical practice and future interventions with women experiencing PND.

## Aims and Objectives

The primary aim of the study is to determine whether usual care plus a pragmatic exercise intervention is superior to usual care only, in reducing PND. The secondary aim is to compare physical activity, quality of life, body weight, BMI, body image and vitality scores between those receiving the exercise intervention plus usual care with those receiving usual care only. A qualitative study will be nested within the trial to explore the acceptability of the intervention to newly delivered women and to illuminate possible reasons for the quantitative findings.

## Methods/Design

### Design and population

This study is a pragmatic two arm randomised controlled trial (individual randomisation) with participants allocated to usual care plus exercise or usual care only. We aim to recruit 208 women with clinically defined postnatal depression (ICD-10 diagnosis of depression). Recruitment will take place between April 2010 and January 2012.

### Inclusion and exclusion criteria

#### Inclusion criteria

· An ICD-10 diagnosis of depression, following screening using the EPDS at 10–14 and 12–16 weeks and CIS-R at 13–17 weeks after giving birth. Women with a mixed diagnosis of anxiety and depression are also eligible

· Aged 18 years or more

· Currently inactive (defined as not meeting the current public health guidelines for physical activity (i.e. <150 minutes of moderate intensity physical activity per week in previous 7 days))

#### Exclusion criteria

· Pregnant at baseline

· Experiencing psychotic symptoms at baseline

· Dependent on illicit drugs or alcohol

· Not proficient in English at a level to complete research assessments

· GP considers patient unsuitable for the trial

· Women whose babies have died

· Women not living with the baby

#### Recruitment of women

##### Patient identification and screening (10–14 weeks after birth)

Recently delivered women who live within South Birmingham and Birmingham East and North Primary Care Trusts (PCTs) are identified from the computerised Child Health System (CHS). This approach allows us to systematically identify all women who have recently given birth and which practices they are registered with in these PCTs. Representatives from the CHS complete searches of new births every two weeks throughout the recruitment period.

Participating GPs/practices are asked to confirm exclusions from the CHS patient lists of new births. Once exclusions are made the CHS mail the trial information letter (on GP practice headed paper) and the Edinburgh Postnatal Depression Scale [25] (EPDS) to women on behalf of the GP/practice. Women are sent this at approximately 10–14 weeks after giving birth and asked to return their completed EPDS to the research team using a prepaid envelope. Non-responders are sent a reminder two weeks later. A brief written overview of the trial is given to women at this stage, but written informed consent is obtained only for the research team to contact women who score >10 on this first EPDS to arrange completion of the EPDS for a second time and the Clinical Interview Schedule-Revised [26] 12–16 weeks after birth (see below). See Figure 1 for trial flow diagram.

**Figure 1 F1:**
[figure not shown]
Trial Flow Diagram.

##### Case definition (home visit at 12–16 weeks after birth)

In order to rule out the possibility of transient depression, women who score >10 on the first EPDS at 10–14 weeks complete a second EPDS about two weeks later at 12–16 weeks by telephone. Women who score >12 on the second EPDS at 12–16 weeks complete a Clinical Interview Schedule-Revised [26] (CIS-R) at a home visit. Based on the information obtained in the CIS-R, women are assessed as being a case according to the ICD-10 depression criteria. Women with a mixed diagnosis of anxiety and depression are also considered a case.

The trial participant information sheet is sent to women at least 2 days prior to the CIS-R home visit and women have already received an information letter from their GP. Women are given the opportunity to ask questions during the home visit before providing written informed consent for the trial. Eligible women complete the baseline questionnaires at the home visit, prior to randomisation.

##### Referral from GPs and health visitors/late onset

Women who present with depression after 10–14 weeks but within 6 months of giving birth are able to enter the trial via referral from their GP or health visitor. Women who are referred in this way have to complete the EPDS twice (as described earlier), the CIS-R, meet the ICD-10 criteria for depression, as well as other trial eligibility criteria as described. Women with a mixed diagnosis of anxiety and depression are also eligible via this route.

##### Baby clinics

In addition to the recruitment strategies outlined above, study leaflets are distributed to women when they attend their practice for baby clinic/check. Baby clinics usually take place at 8, 12 and 16 weeks after birth in England. If women indicate an interest in the study as a result of reading the leaflet they are asked to complete the EPDS screening questionnaire and reply form. These women complete all the screening processes as previously described and have to meet the ICD-10 criteria for depression.

#### Outcomes and allocation of participants to trial groups

##### Primary outcome

The primary outcome measure is the difference in mean EPDS [25] score between the groups at 6 month follow-up (end of the intervention).

#### Secondary outcomes

Quality of life is determined using the SF-12 [27] and EQ-5D questionnaire [28]. Body image is assessed using subscales from the Maternal Adjustment and Maternal Attitudes Questionnaire (MAMA) [29]. Vitality is measured using the Subjective Vitality Scale [30]. Perceived social support and social networks are assessed using items from the 2000 Office of National Statistics Survey of the mental health of households in Great Britain [31]. The Social Support for Physical Activity Scale [32] and the Self-efficacy Scale for Exercise [33] are completed by participants. Physical activity is measured objectively using accelerometers (in a 50% random sub-sample) and subjectively using the IPAQ-short [34]. Body weight and height are assessed objectively. Adverse events resulting from the intervention are systematically recorded.

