#### Assessment of outcomes and blinding

A distant internet randomisation service is used to allocate women to the trial groups. The research team informs women of their allocation after completion of the baseline assessment at the home visit. The randomisation is stratified by baseline EPDS score (13–16 or ≥16). At baseline we collect demographic data; this includes age, marital status, ethnicity, social class, parity, method(s) of infant feeding, history of psychiatric illness, referral(s) to psychiatric and/or mental health services, mode of delivery, level of social support, current medication and pregnancy and antenatal exercise patterns as well as all the outcome measures.

Outcome measures will be assessed at baseline, six months (immediately post intervention) (primary) and 12 months post randomisation. At baseline, the questionnaires (see exception below) are completed and weight is assessed at the home visit. Those randomised to wear the actiheart have the device fitted at the home visit and are asked to wear it for three consecutive days. The research team collect the actiheart from participants and the IPAQ is then completed.

At follow ups, the questionnaires are mailed to all participants at the appropriate time and collected by home visits from the research team. Weight is also measured at the follow up home visits. Those wearing the actiheart have the device fitted at the home visits, are asked to wear it for 3 consecutive days and then complete the IPAQ.

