#### Process outcomes/adherence

Participants randomised to the exercise intervention group are asked to complete exercise diary logs that detail the dose/amount and type of exercise completed during weeks 4, 8, 12, 16, 20 of the intervention. Logs are completed with the PAF either in person or over the phone or sent and returned by post.

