### Analysis plan

Baseline characteristics of participants will be tabulated by randomisation arm. Primary analysis will compare mean EPDS score at the 6 months follow-up between trial groups, adjusting for baseline scores using analysis of covariance. Similar analyses will be conducted for the secondary outcomes. Secondary analyses will adjust for covariates (e.g. age, gender, initial weight, ethnicity, education level) again using analysis of covariance. To explore any longer term effects, a repeated measures mixed model analysis of the primary and secondary outcomes will be undertaken, comparing groups across the 6 and 12 month time points. EPDS score taken at the home visit will be used as the baseline score in analyses. We will also report data on the proportion of women in each group who score less than 13 points on the EPDS at follow-up. All analysis will be by intention to treat.

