#### Usual care

There is no interference with usual care. The GP and patient can decide on any additional treatments. The usual care only group is sent the study “Looking after yourself” leaflet at baseline and exercise is not further encouraged beyond receipt of this single leaflet. Women in the usual care group will be offered an exercise consultation at the end of their involvement in the study.

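### The adverse-event outcome is defined by attribution to the intervention, so recorded events cannot be compared between the exercise and usual-care arms

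*Protocol article*

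**What the plan says.** Adverse events appear once in the protocol article, as the last sentence of Secondary outcomes: "Adverse events resulting from the intervention are systematically recorded". No other section gives a rule for recording events whatever their cause, or for recording them in the usual-care arm.

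The comparison is described under Design and population as "participants allocated to usual care plus exercise or usual care only". Under Usual care, the control group is sent one leaflet at baseline, and "exercise is not further encouraged beyond receipt of this single leaflet". The only other exposure planned for that group comes after follow-up: "Women in the usual care group will be offered an exercise consultation at the end of their involvement in the study".

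For the outcomes listed under Secondary outcomes, the Analysis plan says "Similar analyses will be conducted for the secondary outcomes", that is, between-group analyses like the one for the primary outcome. Both arms are seen at follow-up: under Assessment of outcomes and blinding, "the questionnaires are mailed to all participants at the appropriate time and collected by home visits from the research team".

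The Background says of the condition under study: "Suicide is a rare but devastating consequence of PND".

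**The concern.** A comparison of harms between randomised arms works only if an event counts in the same way in each arm. A definition that requires the event to have been caused by the intervention does not meet that condition. It admits events in the exercise arm after a causal judgement and shuts out nearly everything in the usual-care arm, whatever happens to the women there.

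The error can run in either direction. A few attributed events set against a forced zero can suggest harm where the underlying rates are equal. Equally, a real excess in the exercise arm can be missed if individual events are put down to other causes, because there is no control rate to reveal the excess.

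This matters because participants have an ICD-10 diagnosis of depression, and the Discussion intends the findings to inform NICE guidance, where benefit has to be weighed against harm. An analysis plan cannot repair the problem later, since events that were never collected cannot be analysed.

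**Working it through.** **Inputs**

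- Recording rule: events attributed to the intervention (Secondary outcomes).
- Control exposure during follow-up: one leaflet (Usual care).
- Numbers: 83 per arm needed and 104 per arm randomised, allowing for 20% dropout at 6 months (Sample size). Check: 83 / 0.80 = 103.75, rounded up to 104; conversely 104 × 0.80 = 83.2.
- Event rates and attribution shares: none stated, so the values in step 2 are assumptions.

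**Step 1: apply the rule to each arm**

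- *Exercise arm.* Recorded count = n × p × s, where p is the all-cause event risk and s is the share of events judged to result from the intervention.
- *Usual-care arm.* During follow-up there is no exercise intervention for an event to result from, so s is essentially 0 and the recorded count is essentially 0 for any p. The word essentially is needed because a leaflet is sent.

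The recorded risk difference is therefore about p × s in the exercise arm minus 0. It depends on s, a causal judgement, and carries no information about p in usual care.

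**Step 2: illustrate with equal true risk in both arms** (n = 104 per arm, p and s assumed)

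| p | s | Recorded, exercise | Recorded, usual care | All-cause, each arm |
|---|---|---|---|---|
| 5% | 25% | 1.3 | 0 | 5.2 |
| 5% | 50% | 2.6 | 0 | 5.2 |
| 10% | 25% | 2.6 | 0 | 10.4 |
| 10% | 50% | 5.2 | 0 | 10.4 |
| 20% | 25% | 5.2 | 0 | 20.8 |
| 20% | 50% | 10.4 | 0 | 20.8 |

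In every row the true difference is zero, so the recorded difference comes wholly from attribution.

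**Step 3: what recording whatever the cause would allow**

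If no events of a given type were seen among n women in an arm, the one-sided 95% upper bound on the risk is 1 − 0.05^(1/n):

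- n = 104: 1 − 0.05^(1/104) = 2.84%, about 2.8%.
- n = 83: 1 − 0.05^(1/83) = 3.5%.

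The second figure is the more relevant one if events are asked about at the 6 month visit and dropout is as assumed.

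**Step 4: what is already comparable**

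The EPDS is the primary outcome, assessed in both arms at baseline, 6 and 12 months, and the Analysis plan also reports the proportion scoring below 13 by group. SF-12, EQ-5D and weight are measured in both arms too. Worsening on any of these can be compared whatever its cause, in the women who are followed up. No measure is stated in either arm for injury, self-harm or admission.

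**The case against.** The strongest reply is that this is a journal article condensing a fuller protocol. The sentence says that attributed events are recorded; it does not say that other events are not. Definitions of serious events, reporting in both arms and relatedness procedures are commonly left to the full document, and their absence here is not a fault. That stands, and it means the article does not show that unattributed events go unrecorded in the trial. It does not remove the point, because the article does more than stay silent: it describes the adverse-event outcome with a causal qualifier, and that qualifier is what makes the arms non-comparable.

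Several stronger readings that a reader might infer are not supported:

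- *That the trial cannot compare harm at all, or that worsening depression goes uncounted.* The EPDS is measured and compared in both arms. The limit concerns adverse events.
- *That attribution is made by someone who knows the allocation.* The article does not say who judges it.
- *That the exercise arm has more chances for events to be picked up.* Intervention contacts exist, and "Participants randomised to the exercise intervention group are asked to complete exercise diary logs", but the logs are described as covering the amount and type of exercise. Nothing says that events are collected at these contacts.
- *That under the present rule nothing can be said after zero events.* Zero attributed events would still bound the risk of attributed events. What is lost is the all-cause bound and the comparison.

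It is also fair that about 100 women per arm could not usefully compare an outcome as rare as suicide under any recording rule, and that the Background names suicide as a consequence of the condition, not of exercise. How much safety data a low-intensity behavioural trial should collect is partly a matter of proportion.

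**Conclusion.** The point holds for recorded adverse events. As the outcome is worded, the usual-care arm can contribute essentially none, so a between-arm comparison of those events is not interpretable, although the Analysis plan's general statement on secondary outcomes would cover it. The conclusion follows from the wording and the description of the two arms and needs no numerical input.

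The size can only be illustrated: about 1 to 10 recorded events against 0, when the true counts are equal at about 5 to 21 per arm, under the assumed rates and attribution shares. The conclusion rests on the article's sentence being the operative definition. If a fuller protocol records serious events and injuries in both arms whatever the cause, the remaining fault is one of wording in the article.

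**What to change.** Reword the adverse-event sentence under Secondary outcomes so that serious adverse events (deaths, self-harm, hospital and psychiatric admissions) and injuries are recorded in both arms whatever the cause. Ask the same questions of every participant at the 6 and 12 month home visits. Record relatedness to the intervention as a separate field, classified afterwards, and report events by arm with relatedness as an additional breakdown. If any events come to light only through intervention contacts, tabulate them separately so that they do not enter the comparison. If the full protocol already does this, the change is to make the sentence agree with it.

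The cost is a few added items at visits that already take place in both arms, and some data handling. No visit is added and no treatment changes.
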